**Methods:**

A total of 30 non-consecutive patients will be selected from our institutional database comprising 3144 cranial CT scans performed for acute stroke symptoms January 2018 to August 2022. The clinical and radiologic data of the 30 patients will be presented in random order to a group of 29 physicians in two separate sessions at least three weeks apart. In each session, the physicians will evaluate each patient once with automated perfusion images and once without. We will use non-overlapping 95% confidence intervals and difference in agreement classification as criteria to suggest a difference between the Gwet AC1 statistics (κ_G_).

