### Survey

Cases will be collected and managed using Microsoft Excel v16.72 and REDCap (Research Electronic Data Capture) electronic data capture tools hosted at the Unity Health- St. Michael’s Hospital. REDCap is a secure, web-based software platform designed to support data capture for research studies, providing 1) an intuitive interface for validated data capture; 2) audit trails for tracking data manipulation and export procedures; 3) automated export procedures for seamless data downloads to common statistical packages; and 4) procedures for data integration and interoperability with external sources [29, 30]. Individual, personalized links were sent to the raters via email. Raters were asked details about their practice: type of hospital affiliation, specialty, years in practice and institutional neuroimaging practices for stroke patients. The full survey is in **S1 Appendix.**

For each of the selected 30 patients the following details will be provided: age, location of occlusion, the NIHSS (National Institutes of Health Stroke Score), time of onset, time of scan, non-perfusion CT neuroimaging (NCCT and CTA). The NCCT scan will be shown in the recommended stroke window settings (35WW 35LL) [31–33]. Doing so ensures that the raters are able to evaluate the scan in a window that is optimized for showing the early ischemic changes important for ASPECTS.

The same 30 cases will be shown again with the same information but with perfusion CT neuroimaging (NCCT, CTA and automated perfusion imaging). Overall, the raters will encounter 60 cases comprised of the same 30 patients shown twice with and without perfusion imaging. The raters will not be informed that these 60 cases are actually the same 30 patients shown twice. To test intra-rater agreement, a second round of rating will be done at least 3 weeks from the submission of the initial reading [34]. The order in which the cases are shown will be the same for the second rating. Apart from not telling the raters, the following measures were also taken to keep the raters realizing that the same 30 cases are being shown:

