Invitation e-mails will have an abbreviated title, “Clinical uncertainty in large vessel occlusion ischemic stroke: An intrarater and interrater agreement study”, instead of, “Clinical uncertainty in large vessel occlusion ischemic stroke: Does automated perfusion scanning make a difference? An intrarater and interrater agreement study”Each case will be presented separately in a single screen. The back button for the survey was disabled; consequently, raters were unable to review their previous answers.A random number generator will be used to determine the order all the cases.

For each case, the raters will be asked to grade the ASPECTS, the single-phase collateral score (collateral score 0: absence of vessels distal to the occlusion, 1: ≤ 50% but >0% collateral supply, 2: ≥ 50% but <100% collateral supply or 3: 100% collateral supply), and finally whether they would recommend EVT based on the available clinical and radiologic data [9, 35]. The ASPECTS (0–10) divides the middle cerebral artery territory into 10 areas and takes a point away for each area that appears to have early ischemic changes. Prior to answering questions pertaining to 60 cases, a short review of the ASPECTS and single-phase CT collateral score was done. **(see S1 Appendix)**

Prior to inviting official study raters, the final version of the survey will be sent to 5–10 physicians who are trainees in the field of stroke neurology and neurointervention. Edits will be made to the survey based on their feedback prior to starting the study with the official raters. The trainees who will participate in the pilot testing are those that do not meet the study’s rater inclusion criteria.

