## Discussion

Findings of this study, together with data on the clinical outcomes of patients triaged using the two imaging modalities and cost effectiveness analysis should provide a complete assessment of the utility of perfusion CT neuroimaging. If the reliability of decisions made by clinicians is not significantly different between the two neuroimaging protocols, then recommendations regarding neuroimaging in the late time window may need to be modified to reflect these results. Our goal is to determine whether the automated perfusion CT images and quantitative values found in the perfusion CT neurimaging protocol add value to clinical decision making from a reliability standpoint.

Our study is limited to CT neuroimaging and will not tackle cranial MRI—a different imaging modality that may also be used in acute stroke. This will limit the findings of our study as perfusion imaging can also be used with cranial MRIs. Our results will only be applicable to Canadian practice as all our raters are from comprehensive academic centers in this country. As a previous study demonstrated, decision-making is different across the globe even with cases that fit high level recommendations (Level 1A and Level 2B) [46]. Our study also involves some degree of deception of our recruited raters. While we have taken several measures to keep the mechanics of the study confidential, they may still figure out that they are viewing the same cases twice each round. This may lead to efforts towards delivering consistent answers.

Knowledge dissemination will be through presentation in conferences dealing with stroke and neurointervention. Afterwards, the results will be published in peer-reviewed journals.

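### Reusing the first-round case order in the second rating biases intrarater AC1 upward by an unknown amount

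*Protocol article*

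**What the plan says.** The Survey section describes one round as follows: "the raters will encounter 60 cases comprised of the same 30 patients shown twice with and without perfusion imaging". For intrarater agreement, "a second round of rating will be done at least 3 weeks from the submission of the initial reading", and then: "The order in which the cases are shown will be the same for the second rating". No reason is given for keeping the order.

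That sentence stands directly before a list of measures meant to stop raters noticing the repeated patients. The measures are a shortened study title, one case per screen, a disabled back button ("The back button for the survey was disabled; consequently, raters were unable to review their previous answers") and a random sequence ("A random number generator will be used to determine the order all the cases"). None of them changes the sequence between rounds.

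The abstract says the data will be "presented in random order to a group of 29 physicians in two separate sessions at least three weeks apart". The Discussion concedes that raters "they may still figure out that they are viewing the same cases twice each round" and adds: "This may lead to efforts towards delivering consistent answers". It says nothing about carry-over from the first round to the second.

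**The concern.** Test-retest agreement should reflect how consistently a physician decides on the same clinical and imaging content. With an identical sequence the two readings share more than that content. A borderline case that follows a very large core, or that comes near the end of 60 screens, meets the same contrast and the same fatigue both times. A familiar sequence is also a cue to earlier answers. Each rater sees each patient four times in all (two versions in each of two rounds), so the opportunity for recognition is real.

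The third study question is about intrarater agreement, and the Agreement statistics section makes the agreement category part of the criterion for a difference. Coefficients raised by a shared sequence would overstate how repeatable these decisions are when patients arrive in no set order.

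**Working it through.** The protocol gives no figure for this effect, so there is none to reproduce. The calculations below establish direction and show a range under stated assumptions.

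**Inputs from the document.** Anticipated agreement 0.6 and anticipated prevalence of an EVT recommendation 0.5 (Sample size); moderate 0.41–0.60 and substantial 0.61–0.80 (Agreement statistics).

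**Assumptions not in the document.** The share r of second-round answers reproduced from the first; the standard deviation (SD) of a position effect; the SD of residual within-rater noise.

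**1. Recall.** If a share r of answers is copied, observed agreement is Pa′ = r + (1 − r)Pa. At prevalence 0.5, AC1 = (Pa − 0.5)/0.5 = 2Pa − 1, so AC1′ = r + (1 − r)AC1.

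| r | True AC1 0.60 reads | True AC1 0.80 reads | Gap (true 0.20) |
|---|---|---|---|
| 0.05 | 0.62 | 0.81 | 0.19 |
| 0.10 | 0.64 | 0.82 | 0.18 |
| 0.20 | 0.68 | 0.84 | 0.16 |
| 0.30 | 0.72 | 0.86 | 0.14 |

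This is total recall. Much of it would occur under any order, and only the part added by the fixed sequence belongs to this point. The table is therefore not an estimate of the defect.

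**2. Position and neighbouring-case effects.** Let a decision be yes when case effect (SD 1) + position effect (SD s) + noise (SD e) exceeds zero. The correlation ρ between the two readings' latent scores is

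- same order: ρ = (1 + s²)/(1 + s² + e²)
- new order: ρ = 1/(1 + s² + e²)

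At prevalence 0.5, AC1 = 2·arcsin(ρ)/π. With e = 0.6:

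| s | ρ same | AC1 same order | ρ new | AC1 new order |
|---|---|---|---|---|
| 0 | 0.735 | 0.53 | 0.735 | 0.53 |
| 0.2 | 0.743 | 0.53 | 0.714 | 0.51 |
| 0.4 | 0.763 | 0.55 | 0.658 | 0.46 |
| 0.6 | 0.791 | 0.58 | 0.581 | 0.40 |

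A simulation of 400,000 draws per setting agrees to within 0.003. At every non-zero s the same order gives the higher coefficient, both against the new order and against the value with no position effect (0.526 before rounding). With s = 0 the order makes no difference.

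**3. The contrast between imaging protocols.** Take e = 0.6 for one protocol and, as a further assumption, e = 0.3 for the other. With no position effect the gap is 0.740 − 0.526 = 0.21.

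| s | Gap, same order | Gap, new order |
|---|---|---|
| 0.4 | 0.757 − 0.553 = 0.20 | 0.590 − 0.457 = 0.13 |
| 0.6 | 0.775 − 0.581 = 0.19 | 0.485 − 0.395 = 0.09 |

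In this model the new order shrinks the gap more than the fixed order does. Under recall, equal r narrows the gap (table 1), while unequal r can create one. With both true values at 0.60, r = 0.20 on perfusion screens and r = 0 on the others, the result is 0.68 against 0.60. The direction for the contrast is not determined.

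**The case against.** The strongest reply is that repeating a measurement under identical conditions is a legitimate repeatability design. The Case selection section frames the aim as repeatability of decisions in an experimental setting, and treating order as a source of variation changes what is estimated. The model supports part of this: for position effects alone, at s = 0.6 the fixed order lies about 0.05 above the value with no position effect, while the redrawn order lies about 0.13 below it. What stands is that redrawing has its own consequence and that the quantity should be named. However, the same section also speaks of reliability in real-world scenarios, where patients do not arrive in a repeated sequence, and the protocol gives no argument for holding the order fixed.

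A second reply is that the interval of at least three weeks, the 60 single-screen presentations and the disabled back button already limit recall. They do, but none of them alters a repeated position or a repeated preceding case.

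Three stronger readings are tempting and are not supported:

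- *The fixed order drives the comparison towards no difference.* That requires equal recall under both protocols, which nothing in the document establishes, and the position model points the other way when the remedy is compared with the present design.
- *The bias lifts results from moderate to substantial.* In the recall illustration this happens because 0.60 is the top edge of the moderate band, so almost any rise crosses it. From 0.50, a recall share of 0.10 gives 0.55 and no change of category.
- *The abstract contradicts the Survey section.* A single randomly generated order used twice is still a random order. The abstract can be misread, but it is not wrong.

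**Conclusion.** The point holds in a limited form. The same sequence in both rounds can only hold or raise intrarater AC1, so under any real position, context or sequence effect the coefficients for both protocols are too high as statements about decisions made in no fixed order. The choice also gives up, between rounds, the benefit of the random ordering that the protocol lists among its masking measures, although the Discussion accepts that recognition pushes raters towards consistency.

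The amount is unknown. The excess of same-order over new-order AC1 runs from 0 with no position effect to about 0.03, 0.10 and 0.19 at s = 0.2, 0.4 and 0.6, and these figures rest wholly on assumed SDs and on prevalence 0.5. The effect on the perfusion versus non-perfusion contrast is of uncertain direction. First-round interrater agreement is not affected by reusing the order in round two.

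**What to change.** Replace the sentence in the Survey section with: *A new random order, generated independently of the first, will be used for the second rating.* One new order common to all raters is enough; separate orders per rater are optional and would mean many more survey versions. The protocol states no minimum separation between the two versions of a patient, so the new wording should not refer to one.

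The cost is one further run of the generator and re-keying the survey once. Order effects then count as within-rater variation. This lowers the coefficients slightly if those effects are small and more if they are large, and the report should say so.

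If the second round has already been run, add the fixed order to the Discussion as a limitation of the intrarater results. Also make clear in the abstract that one random order served both sessions.

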### Rater selection

We will invite physicians who are practicing stroke neurologists and neurointerventionalists in Canada who work in comprehensive stroke centers with access to perfusion imaging. These specialties will be chosen because in the typical clinical pathway these physicians are ultimately responsible and decide whether an ELVIS patient undergoes EVT. While diagnostic neuroradiologists with no neurointervention training are certainly a vital part of the stroke team, they are limited to interpreting imaging or making suggestions for patient management. Invitations will be sent to the physicians through the Canadian Stroke Consortium and the Canadian Interventional Neuro Group. By tapping into these national societies, we hope to include a group of raters with diverse background and differing levels of experience from different parts of the country. The inclusion criteria for the raters will be as follows:

Currently practicing in Canada as a stroke neurologist or neurointerventionalistBased out of a comprehensive center that offers EVTHaving completed at least 1 year of fellowship in stroke neurology or neurointervention

Clinical fellows will be allowed to participate in the study if they had already finished at least a year of fellowship. These individuals are considered to be junior attendings. While no monetary incentive was provided, the invitation will state that all those who finish both rounds of the survey will be given the opportunity to be a co-author in future publications if they wish. All those with equal to or more than 10 years of experience (post-residency training) will be considered senior raters—the rest will be junior raters. Neurointervenitonalists are physicians who are trained in performing EVT. Stroke neurologists, neuroradiologists and neurosurgeons can all undertake fellowship training to become neurointervenitonalists. Our raters will be classified as: stroke neurologists, neurointerventionalists (neuroradiologists and neurosurgeons) and dual-trained neurologists who are both stroke neurologists and neurointerventionalists. After the study, all raters will be sent a debriefing letter to explain the deception involved in the research. They will all be given a chance to withdraw from the study.

### Sample size

We estimated, using kappaSize package in R version 4.2.0 (R Foundation for Statistical Computing, Vienna, Austria), assuming an anticipated kappa value of 0.6 (substantial), that at least 30 cases were necessary for the lower limit of a 95% two–sided confidence interval to remain above 0.45 between at least 6 raters, considering an anticipated prevalence of EVT recommendation of 0.5 [36]. A rule of thumb for agreement studies with binary outcomes is to have at least 10 raters reviewing at least 30–50 patients [25]. While more patients will enable us to provide an even wider spectrum of patients we also want to avoid rater fatigue. For this study we had 60 cases with three questions each. We need to have at least 6 raters based on our sample size computation but will be aiming for at least 10 to follow the current convention.

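### The stated precision (two-sided 95% lower limit above 0.45 with 30 cases and 6 raters) is not reproduced under two common binary agreement models, and kappa 0.6 is labelled against the protocol's own scale

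*Protocol article*

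**What the plan says.** The Sample size section gives a complete set of inputs for one precision statement.

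- Software: "We estimated, using kappaSize package in R version 4.2.0".
- Anticipated agreement: "assuming an anticipated kappa value of 0.6 (substantial", with that word in brackets as the label.
- Target: "at least 30 cases were necessary for the lower limit of a 95% two–sided" "confidence interval to remain above 0.45 between at least 6 raters".
- Prevalence: "considering an anticipated prevalence of EVT recommendation of 0.5".

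Six raters is the computed minimum. The authors "will be aiming for at least 10 to follow the current convention", and the abstract's Methods paragraph speaks of "a group of 29 physicians in two separate sessions at least three weeks apart".

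The Agreement statistics section names Gwet's AC1 as the coefficient. Its classification puts 0.41 to 0.60 as moderate and 0.61 to 0.80 as substantial.

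**The concern.** This is the only precision statement in the article, and all its inputs are printed, so it can be checked. The two usual ways of writing down correlated binary ratings from six raters both give more than 30 cases for a two-sided 95% limit of 0.45. If the sentence is wrong as printed, the reader is told that the interrater coefficient will be estimated more tightly than it will be at the stated minimum.

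The label is a separate slip that needs no modelling. It matters a little because the agreement category is one of the two criteria the protocol uses to suggest a difference between coefficients.

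**Working it through.** **Inputs (all from the Sample size section).** Kappa 0.6, lower limit 0.45, 6 raters, prevalence 0.5, 95% two-sided, stated result 30 cases.

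**Method 1: goodness of fit, 1 degree of freedom.** Let P_j(κ) be the probability that j of 6 raters recommend EVT for a case. The cases needed are

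n = c / S, with S = Σ_j [P_j(0.6) − P_j(0.45)]² / P_j(0.45),

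where c = 3.8415 (two-sided 95%) or 2.7055 (one-sided 95%, that is two-sided 90%). Kappa, prevalence and the number of raters do not fix P_j, so three models were tried.

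*Mixture common-correlation:* P_j(κ) = (1−κ)·C(6,j)/64, plus κ/2 when j = 0 or 6.

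| j | P_j(0.6) | P_j(0.45) | term |
|---|---|---|---|
| 0 and 6, each | 0.3063 | 0.2336 | 0.0226 |
| 1 and 5, each | 0.0375 | 0.0516 | 0.0038 |
| 2 and 4, each | 0.0938 | 0.1289 | 0.0096 |
| 3 | 0.1250 | 0.1719 | 0.0128 |

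S = 2(0.0226 + 0.0038 + 0.0096) + 0.0128 = 0.0848. Two-sided: 3.8415/0.0848 = 45.3, so 46 cases. One-sided: 2.7055/0.0848 = 31.9, so 32.

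*Beta-binomial:* both parameters equal (1−κ)/(2κ), which is 0.333 at κ = 0.6 and 0.611 at κ = 0.45. S = 0.1031. Two-sided: 37.3, so 38. One-sided: 26.3, so 27.

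*Symmetric two-class latent model:* half the cases have recommendation probability 0.5 + d and half 0.5 − d, with d = 0.5√κ (0.387 at κ = 0.6, 0.335 at κ = 0.45). S = 0.1221. Two-sided: 31.5, so 32. One-sided: 22.2, so 23.

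**Lower limit reached with 30 cases.** Solve 30·Σ_j [P_j(0.6) − P_j(κ_L)]²/P_j(κ_L) = c for κ_L, with 6 raters.

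| Model | two-sided 95% | one-sided 95% |
|---|---|---|
| Mixture | 0.417 | 0.445 |
| Beta-binomial | 0.434 | 0.459 |
| Two-class latent | 0.446 | 0.471 |

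**Method 2: Wald interval.** At prevalence 0.5 the chance term of AC1 is 0.5, so the coefficient is 2·(mean pairwise agreement) − 1 and SE = 2·SD(agreement per case)/√30. A lower limit of 0.45 requires SE = 0.15/1.96 = 0.0765.

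- Mixture: SE 0.0943; 0.6 − 1.96 × 0.0943 = 0.415; 46 cases needed.
- Beta-binomial: SE 0.0862; limit 0.431; 39 cases needed.
- Two-class latent: SE 0.0754; limit 0.452, just inside the target.

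**More raters, still 30 cases, two-sided, goodness of fit.**

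| Raters | Mixture | Beta-binomial |
|---|---|---|
| 6 | 0.417 | 0.434 |
| 10 | 0.423 | 0.459 |
| 29 | 0.423 | 0.486 |

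**Label.** The value 0.6 lies in the band 0.41 to 0.60, which the Agreement statistics section calls moderate. Substantial begins at 0.61.

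The kappaSize package itself was not run.

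**The case against.** The strongest reply is that the result depends on a model the article does not print, and that the named package was not run. This stands. The two-class latent model nearly meets the target by goodness of fit and meets it by the Wald interval. An extreme pattern, in which raters are unanimous or exactly one dissents, would need only 19 cases. A normal-theory intraclass formula gives 1 + 2(1.96²)(0.4²)(1 + 5 × 0.6)²/(6 × 5 × 0.15²) = 30.1 two-sided, but it is for continuous ratings and ignores prevalence. The figure of 30 is therefore not shown to be impossible.

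A reader might go further in three directions that the documents do not support.

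- *That only a one-sided bound can explain 30.* The one-sided value brackets 30 under two models (27 and 32) but hits it under neither. The call is not shown, so this is an inference.
- *That the calculation fails the between-protocol and intrarater questions.* The section describes the precision of one interrater kappa and claims nothing about differences or intrarater agreement. Precision for further comparisons may sit in the full protocol or analysis plan.
- *That 29 raters contradicts 6.* Six is a floor and at least 10 is the aim; 29 satisfies both.

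It is also fair to say that the shortfall is small and applies at a number of raters the study plans to exceed. Under the beta-binomial model the target is met with 10 raters; under the mixture model it is not met even with 29.

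**Conclusion.** The concern holds in a limited form. The two-sided 95% statement for 30 cases and 6 raters is not reproduced under the mixture or beta-binomial model, which need 46 and 38 cases. The lower limit at 30 cases is about 0.42 to 0.43, some 0.02 to 0.03 below the stated 0.45. This rests on kappa 0.6, prevalence 0.5 and those joint distributions; a two-class latent model narrows the gap to about 0.004 or closes it. A one-sided bound is a plausible but unconfirmed explanation. The mislabelling of 0.6 holds without assumptions. Neither point shows that 30 cases is the wrong size for the study.

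**What to change.** Check the kappaSize call, then restate the sentence without adding cases.

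- If a one-sided bound was computed, say that the one-sided 95% (two-sided 90%) lower limit is about 0.45.
- Otherwise, give a two-sided 95% lower limit of about 0.42 to 0.43 for 30 cases and 6 raters, and name the model.
- Recompute the limit for the number of raters actually planned.
- Describe 0.6 as moderate, in line with the Agreement statistics section.

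The cost is a text correction and one rerun of the calculation. The downside is that the stated precision becomes slightly less favourable.
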